### Other data to be collected

Other data to be collected will include:

1. Baseline data; collected at recruitment before the commencement of the intervention in both the control and intervention arms. Baseline data will include:

1.a. Knowledge, attitudes and practices regarding maternal and infant feeding.

1.b. Maternal anthropometric measurements.

1.c. Household food security.

1.d. Maternal socio-demographic characteristics and socio-economic status.

2. Child motor development (self-reported by the mother using questionnaire); updated every two months during the follow-up period after delivery.

3. Dietary intake for the mother collected every two months during the follow-up period through an interviewer administered questionnaire to the mother.

4. Maternal weight, monitored every two months during pregnancy and in the first year after delivery.

5. Contextual data, including morbidity from common childhood illnesses, antenatal care, place of delivery, vaccination, household food security, water and sanitation and hygiene practices will be collected through an interviewer administered questionnaire to the mother; updated every two months (where relevant) during the follow-up period.

### Before, during and after qualitative studies

In a formative study, in-depth interviews (n = 20), key informant interviews (n = 10) and focus group discussions (n = 10) will be conducted before the beginning of the intervention. In-depth interviews and focus group discussions will be conducted with women of reproductive age who are either pregnant, breastfeeding or have ever breastfed. Additional focus group discussions will be conducted with CHWs and village elders. Key informant interviews will be conducted among health care providers, traditional birth attendants and community leaders. The interviews will be conducted to establish the knowledge, attitudes and practices regarding breastfeeding and complementary feeding and to establish the local contexts and norms, which contribute towards decision-making for MIYCN practices. This information will inform the design of the intervention quantitative tools for assessing the main study outcomes.

As part of process evaluation, qualitative data will also be collected during the intervention and at the end of intervention to document experiences of adhering to optimal MIYCN practices emphasized in the intervention, and satisfaction with the intervention, challenges and enabling factors, and recommendations for change/future practice. This will be collected through in-depth interviews with mothers (approximately seven interviews), and focus group discussions with CHWs (two focus group discussions) at each point in time.

### Statistical analysis

Determination of change for the primary outcome (exclusive breastfeeding) will be done at month six. Difference in duration of exclusive breastfeeding will also be determined longitudinally up to six months between the intervention and control groups. Comparison for other outcomes such as morbidity from diarrhea and malnutrition will be done longitudinally at around month three, six, nine and twelve. Analyses will involve a comparison of differences in the intervention and control groups with regard to the primary outcome (exclusive breastfeeding) and secondary outcomes (other infant feeding practices, diarrhea morbidity and nutritional outcomes), controlling for baseline measures (for example, previous breastfeeding practices) and prognostic factors (for example, Socio-economic status (SES) and household food security) if randomization of the clusters does not control for differences in these factors at baseline. Statistical methods to determine change will include analysis of covariance (ANCOVA) for continuous variables (for example, duration of exclusive breastfeeding and any breastfeeding and multinomial logistic regression analysis for categorical variables (that is, whether exclusively breastfed for six months or not) [40]. Additionally, survival analysis (proportional hazard analysis) for variables measured longitudinally (for example, duration of breastfeeding and malnutrition and multilevel modelling for repeated measures such as diarrheal morbidity will be applied. Intention-to-treat analysis [41] will be applied as appropriate. Efforts will be made to maximize follow-up of participants, using the NUHDSS framework to minimize missing information. Quantitative data analysis will mostly be done using Stata version 12.1. (StataCorp LP, College Station, Texas, USA). (See Table 2 for detailed outline of data analysis plan).

**Table 2 T2:** Data analysis outline

**Study objective**	**Outcome variables**	**Independent variable**	**Control variables**	**Type of analysis**
1. To determine the effect of the intervention on breastfeeding and complementary feeding knowledge, attitudes and practices among mothers of infants	1. Knowledge and attitude levels on breastfeeding and other infant feeding practices	Intervention status	SES^1^, food security, maternal demographic characteristics, antenatal care child morbidity	Multinomial logistic regression for rates and survival analysis for duration
	2. Breastfeeding practices, including initiation of breastfeeding within one hour of birth, exclusive breastfeeding (for first 6 months) and duration of exclusive and any breastfeeding			
	3. Complementary feeding practices for example, optimal timing of initiation of complementary feeding and minimum dietary diversity, minimum meal frequency, and minimum acceptable diet			
2. To determine the effect of the intervention on nutritional outcomes among infants;	1. Stunting	Intervention status	SES, food security, maternal demographic characteristics, child morbidity, antenatal care, vaccination status	Multinomial logistic regression
	2. Underweight			
	3. Wasting			
3. To determine the effect of the intervention on morbidity from diarrhoea among infants	Diarrhoea morbidity	Intervention status	SES, food security, maternal demographic characteristics, child morbidity, antenatal care, vaccination status	Multilevel modeling
4. To determine the experiences, facilitating and limiting factors associated with the intervention	1. Client satisfaction	Not applicable	Not applicable	Descriptive (Outcome 1) Qualitative-thematic analysis (outcomes 2 and 3)
	2. Experiences			
	3. Limiting and enabling factors			
5. To assess the cost-effectiveness of the intervention	Cost-effectiveness	Not applicable	Not applicable	Cost-Effective Analysis

^1^SES=Socio-economic status.

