### Study design and randomization

The study will adopt a cluster-randomised trial design [26,27]. For pragmatic purposes, community units (CUs), defined by the Government’s Community Strategy, will be used as the clusters. Fourteen CUs have been defined in the study areas: eight in Korogocho and six in Viwandani. These CUs will be randomised with half allocated to the intervention and the other half to the control arm. The random sequence of allocation of the CUs to the intervention or control arm will be computer-generated. The clusters will be stratified with regard to two aspects before randomization: slum of residence (Korogocho and Viwandani) and number of women of reproductive age in each cluster: large clusters and smaller clusters. Those in the same slum and in the same strata with regard to size will be randomly allocated to either intervention or control group. Cluster randomization is preferred over individual-level randomization to minimize contamination and for pragmatic purposes in case of future scale-up of the intervention. Randomization will be done by a data analyst who is not a primary member of the study team.

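### Covariate adjustment hangs on an undefined imbalance condition that Table 2 does not share, and neither place includes the stratification factors

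*Protocol article*

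**What the plan says.** Three places in the protocol article bear on this.

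- **Statistical analysis, text.** The arms are to be compared on primary and secondary outcomes, "controlling for baseline measures (for example, previous breastfeeding practices) and prognostic factors (for example, Socio-economic status (SES) and household food security"), but only "if randomization of the clusters does not control for differences in these factors at baseline". No criterion for imbalance is given, and the covariates are introduced as examples. The limitations paragraph of the Discussion follows the same reasoning: adjustment is the answer to chance imbalance.
- **Table 2**, to which the text refers for the detailed analysis outline. Objective 1, which contains exclusive breastfeeding for six months, has the control variables "SES^1^, food security, maternal demographic characteristics, antenatal care child morbidity". Objectives 2 and 3 have "SES, food security, maternal demographic characteristics, child morbidity, antenatal care, vaccination status". No imbalance condition is attached to either list.
- **Study design and randomization.** Allocation is stratified, and the two factors used are given as "slum of residence (Korogocho and Viwandani) and number of women of reproductive age in each cluster: large clusters and smaller clusters". On the number of units the section states: "Fourteen CUs have been defined in the study areas: eight in Korogocho and six in Viwandani", with half of the units allocated to each arm.

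**The concern.** There are two linked problems.

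First, the primary model is not fixed. Under the text it may be adjusted or unadjusted, depending on an undefined judgement of balance. Under Table 2 it is adjusted regardless. The covariates differ too: previous breastfeeding practice is in the text but not in the table, while antenatal care and child morbidity are in the table but not in the text. A covariate is worth including because it predicts the outcome, and looking unbalanced after randomisation is a poor substitute for that. With no criterion and no closed list, the model could be settled once results are visible.

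Second, the two factors that governed the allocation are in neither list. Stratified allocation removes between-stratum variation from the true error of the comparison. An analysis that allows for clustering but ignores the strata leaves that variation in the estimated error. If the strata predict feeding practice, the interval is then too wide and the test conservative. With only 14 clusters, that loss could matter.

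**Working it through.** **Reproducing the plan's figures.** Inputs from Sample size considerations: 2% v 12%, two-sided 5%, power 80%, ICC 0.05, design effect 3.2, attrition 20%.

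- Per arm, unpooled: (1.960 + 0.842)² × (0.02×0.98 + 0.12×0.88) / 0.10² = 98.3, so 196 to 198 in total (stated: 196).
- 196 × 3.2 = 627; 627 / 0.80 = 784 (stated: about 780).
- 627 / 14 = 44.8 analysed per cluster; 1 + 0.05 × 43.8 = 3.19, matching the stated 3.2.

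**What the strata could be worth.** This is an illustration. It takes a linear analysis of cluster means, 7 v 7, and assumes four slum-by-size strata (the documents do not give their number or sizes).

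- Between-cluster share of the variance of a cluster mean: 0.05 × 44.8 / 3.19 = 0.70.
- SE without strata: √[(0.0196 + 0.1056) × 3.19 / 44.8 / 7] = 0.0357. Non-centrality 0.10 / 0.0357 = 2.80; 12 df, t = 2.179; power 73%.
- With strata: SE multiplied by √(1 − 0.70 × R²), where R² is the assumed share of between-cluster variance that the strata explain; 14 − 2 − 3 = 9 df, t = 2.262. The CI ratio is the SE ratio × 2.262 / 2.179.

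| R² (assumed) | SE ratio | CI ratio | Power with strata |
|---|---|---|---|
| 0% | 1.00 | 1.04 | 70% |
| 5% | 0.98 | 1.02 | 72% |
| 10% | 0.96 | 1.00 | 73% |
| 30% | 0.89 | 0.92 | 80% |
| 50% | 0.81 | 0.84 | 87% |

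**Cross-check by simulation**, with assumed strata of 4, 4, 4 and 2 clusters. Here the strata's share is expressed on the whole cluster-mean variance, so 30% of between-cluster variance corresponds to about 0.70 × 30% = 21%. At 20%, power is 74% without strata and 80% with them. Type I error without strata is 5.1%, 3.9%, 2.9%, 1.9% and 0.6% at shares of 0%, 10%, 20%, 30% and 50%. With strata it stays at about 5.0%.

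**What the imbalance condition could do.** Simulation under the null with three assumed cluster-level covariates:

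- Mechanical rule, adjusting for covariates with an imbalance p-value below 0.05: triggered in 13% to 15% of trials. Below 0.20: 47% to 49%. Type I error is 3% to 5% in both.
- Free choice among models after seeing results: type I error 10% to 12%.

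**Room for covariates.** Expected primary events: 627 / 2 × (0.02 + 0.12) = 43.9, about 44. Arm plus three stratum terms makes 4 terms, or 11 events per term. With 4 to 6 more covariates there are 8 to 10 terms, or 5.5 down to 4.4 events per term.

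**The case against.** The strongest reply is that the omission of the strata is read from a condensed article. An analysis plan that is not shown could add them, and nothing in the article forbids it. That limits the second half of the point. It does not dispose of it, because Table 2 is a stated control list, offered as the detailed outline, and neither factor is on it. Nor does it touch the condition in the text or the disagreement between text and table.

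The precision argument also has limits, and these stand:

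- It holds only for an analysis that accounts for clustering. For the binary primary outcome the article names multinomial logistic regression and does not state how clustering enters. It mentions multilevel modelling for repeated measures such as diarrhoea.
- The percentages belong to a linear cluster-level analysis. They do not carry over directly to an odds ratio, which itself changes meaning on adjustment.
- The explained share is assumed. Below about 10%, including the strata costs a little.

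A reader might infer that the imbalance rule inflates type I error. It does not if applied mechanically, and balance in recruitment variables can be judged without outcome data. The 10% to 12% figure requires free choice after results are seen, which the article does not say will happen. A reader might also infer that chance would trigger adjustment in most trials. Such a figure needs individual-level significance tests, independent covariates and the outcome's design effect applied to each of them; the article specifies none of these.

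**Conclusion.** The point stands in limited form. The article states an adjustment rule with no criterion and an open covariate list, and Table 2 contradicts it by listing controls unconditionally. More than one primary model is therefore compatible with the plan. The weakness is that open choice; no inflation of type I error has been shown.

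The stratification factors are absent from both places. It would go too far to say that the plan certainly wastes precision. In an analysis that respects clustering, the consequence runs from a small gain by omission (73% v 70% power if the strata explain nothing), through break-even near 10%, to a material loss (73% v about 80% at 30%). These figures rest on ICC 0.05, about 45 analysed per cluster, four assumed strata and a linear cluster-level analysis. The documents do not say where in the range this trial lies.

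**What to change.** 1. Delete the condition in the Statistical analysis text that ties adjustment to the result of randomisation.
2. Fix one primary model: arm, slum and cluster-size stratum, in an analysis that accounts for the 14 clusters and their small number.
3. Add at most a very short, named list of covariates measured at recruitment (item 1 of Other data to be collected), included whatever the observed balance. About 44 expected events leave little room. Restricting to recruitment matters because Table 2 also lists antenatal care, child morbidity and vaccination, which item 5 of the same section has updated during follow-up.
4. Make the text and the control-variable column of Table 2 agree.

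The cost is mainly wording; sample size and conduct do not change. The statistical downside is up to about 3 of 12 cluster degrees of freedom (with four strata), or about 3 points of power if the strata explain nothing.

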**Methods/Design:**

The study, employing a cluster-randomised study design, will be conducted in two slums in Nairobi: Korogocho and Viwandani where 14 community units (defined by the Government’s health care system) will form the unit of randomization. A total of 780 pregnant women and their respective child will be recruited into the study. The mother-child pair will be followed up until the child is one year old. Recruitment will last approximately one year and three months from September 2012 to December 2013. The mothers will receive regular, personalised, home-based counselling by trained Community Health Workers on MIYCN. Regular assessment of knowledge, attitudes and practices on MIYCN will be done, coupled with assessments of nutritional status of the mother-child pairs and diarrhea morbidity for the children. Statistical methods will include analysis of covariance and multinomial logistic regression. Additionally, cost-effectiveness analysis will be done. The study is funded by the Wellcome Trust and will run from March 2012 to February 2015.

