To address the problem of child malnutrition, the Kenyan Government developed a strategy in 2007, mirroring the WHO/UNICEF global strategy for IYCN, aimed at promoting optimal IYCN practices in the country [9,17]. The strategy is implemented mainly through the BFHI, which promotes breastfeeding in maternity wards around the time of delivery. Although there has been some improvement in the proportion of children exclusively breastfed in the last few years, the impact of this hospital-based initiative in low-income countries like Kenya is questionable. This is because most women, especially the poor, deliver at home and IYCN practices are greatly influenced by traditional beliefs and practices [13,18]. For example, in Kenya, only 42% of women deliver in health facilities, and this has not changed much in the last 20 years [13].

Urban poor settlements are expanding at an alarming rate in SSA, with the majority of urban residents living in slum settlements [19], thus presenting a unique challenge with respect to implementing the IYCN strategy in Kenya. These slums have been marginalized with regard to provision of Government services; hence public health facilities are rare. Additionally and consequently, a substantial proportion of slum women do not deliver at health facilities, while others deliver in sub-standard private health facilities; only 48% deliver in facilities with skilled birth attendants [20,21]. This means that many of these women do not benefit from the counselling on IYCN offered through BFHI. Findings from studies done in the urban slums of Nairobi indicate high levels of suboptimal MIYCN practices and malnutrition. For example, only two per cent of infants are exclusively breastfed for the first six months, while 15% of infants stop breastfeeding by the end of one year [22]. Furthermore, about four in ten children under the age of five are stunted [23]. This level of malnutrition in an urban setting may not entirely be due to poverty but may reflect practices that might be addressed with proper counselling and advice.

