### Assessment

#### *Outcome measures*

##### 

**Primary outcomes** The primary outcome measure is exclusive breastfeeding for six months.

This will involve determining the change in the rate of exclusive breastfeeding for the first six months. Mothers will be advised on what they need to do with regard to breastfeeding and how they should do it, including breast positioning and attachment and expressing and storing breast milk. This advice is expected to lead to self-efficacy with regard to breastfeeding, hence adherence to WHO guidelines on breastfeeding, resulting in improved rates of exclusive breastfeeding for six months. Data on breastfeeding practices will be collected longitudinally from birth every two months through an interviewer-administered questionnaire to the mother. Self-reported exclusive breastfeeding will be validated on a 10% sample using the stable isotope technique (dose-to-the mother of deuterium oxide) for breast milk analysis. The 10% sample will be randomly selected from the list of participating breastfeeding mothers. The procedure will be carried out once per mother-child pair, sampled before the child is aged six months.

##### 

**Secondary outcomes** Secondary outcomes include:

1. Breastfeeding and complementary feeding knowledge and attitudes according to WHO recommendations [9]. Data will be collected every two months following recruitment through an interviewer-administered questionnaire to the mother to determine change in knowledge, attitudes and practice with the intervention.

2. The duration of any breastfeeding in months.

This will include duration of any breastfeeding in months. Data will be collected longitudinally every two months following birth through an interviewer-administered questionnaire to the mother to determine if the child is still breastfeeding, and if so, whether they have started feeding on other foods/fluids other than breast milk; when they started on other foods/fluids; and if they stopped breastfeeding, when they stopped.

3. Complementary feeding practices.

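### Duration of any breastfeeding is assigned to ANCOVA as well as survival analysis, although about 85% of these durations will still be running at 12 months and Table 2 lists survival analysis only

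*Protocol article*

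**What the plan says.** The Statistical analysis section of the protocol article lists "analysis of covariance (ANCOVA) for continuous variables (for example, duration of exclusive breastfeeding and any breastfeeding" among the methods for determining change. The following sentence reads "Additionally, survival analysis (proportional hazard analysis) for variables measured longitudinally (for example, duration of breastfeeding and malnutrition". The text does not say which of the two is the main analysis.

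Table 2 gives the type of analysis for the first objective as "Multinomial logistic regression for rates and survival analysis for duration". The outcomes under that objective include "duration of exclusive and any breastfeeding". ANCOVA does not appear in Table 2.

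Three other statements bear on the choice:
- Outcome measures lists as a secondary outcome "The duration of any breastfeeding in months", with no upper limit or time horizon.
- The abstract states "The mother-child pair will be followed up until the child is one year old".
- The Background reports for these slums that "15% of infants stop breastfeeding by the end of one year".

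Exclusive breastfeeding, by contrast, has a stated window: "Difference in duration of exclusive breastfeeding will also be determined longitudinally up to six months between the intervention and control groups".

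**The concern.** ANCOVA compares means of an outcome whose value is known for every child analysed. Duration of any breastfeeding will not be known for most children, because observation stops at 12 months while most are still breastfed. Someone must then decide what number to enter for a child still breastfed at 12 months, and for a child lost before that. The article does not fix either choice, and the choices answer different questions.

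At stake is a listed secondary outcome. With two methods in the text and one in the table, a result could be reported from whichever method looks better. With ANCOVA, the answer also depends on the coding of censored children and on how loss to follow-up falls between arms.

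**Working it through.** **Inputs from the protocol article.** Stopped any breastfeeding by 12 months: 15% (Background). End of follow-up: age one year (abstract). Attrition allowance: 20% (Sample size considerations). Exclusive breastfeeding for six months: 2% at baseline, 12% at target (same section). The article states no censoring fraction, so there is no figure of its own to reproduce on this point.

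**Assumptions.** Constant stopping hazard; loss independent of stopping, at a constant rate, with the full 20% falling in the 12 months after birth.

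**Step 1: censoring of any breastfeeding.**
- With complete follow-up, 1 − 0.15 = 85% are still breastfed when observation ends. If the stopping share were 10% to 20%, this would be 90% to 80%.
- With 20% attrition, the stopping hazard is λ = −ln(0.85)/12 = 0.01354 per month and the loss hazard is μ = −ln(0.80)/12 = 0.01860 per month.
- Observed stops: λ/(λ+μ) × (1 − 0.85 × 0.80) = 0.421 × 0.32 = 13.5%.
- Censored: 86.5%, made up of 68% at 12 months (0.85 × 0.80) and 18.5% lost earlier.

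**Step 2: ANCOVA with children still breastfed coded as 12 months, full follow-up.** The mean is (1 − e^(−12λ))/λ.
- 85% still breastfed: 0.15/0.01354 = 11.08 months.
- 90% still breastfed: λ = −ln(0.90)/12 = 0.00878; 0.10/0.00878 = 11.39 months.
- Difference 0.31 month, where the hazard ratio is ln(0.90)/ln(0.85) = 0.65.
- Halving the stopping hazard moves the mean only from 11.08 to 11.53, a difference of 0.45 month.

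**Step 3: ANCOVA with last observed time entered as the duration, no true effect.** The mean recorded time is (1 − e^(−12(λ+μ)))/(λ+μ), with λ as for 85% in both arms.
- 20% attrition: 9.96 months, against 11.08 with full follow-up.
- 15% attrition: 10.24 months. 25% attrition: 9.66 months. The spurious difference is 0.58 month.
- For a smaller imbalance, 18% v 22%, it is 10.07 v 9.84, or 0.23 month.

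The 0.58 month exceeds the true difference from halving the hazard in step 2.

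**Step 4: exclusive breastfeeding to six months.** The share reaching the cap is about 2% (baseline) to 12% (target).
- At 2%: λ = −ln(0.02)/6 = 0.652; capped mean 0.98/0.652 = 1.50 months, uncapped 1.53.
- At 12%: λ = −ln(0.12)/6 = 0.353; capped mean 0.88/0.353 = 2.49 months, uncapped 2.83.
- Spurious difference from 15% v 25% attrition over 12 months, at the 2% baseline: about 0.02 month.

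The difficulty is therefore specific to duration of any breastfeeding.

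**The case against.** The best defence is that the suitable analysis is already planned. Proportional hazards follows in the very next sentence, Table 2 assigns survival analysis to both durations, and the text calls that table the detailed outline. ANCOVA could be a supplementary comparison of means, and the coding of censored values is commonly left to an analysis plan. This largely stands: survival analysis is not missing, and the article's silence on coding is not itself a fault. What remains is that the text names ANCOVA for an outcome that the article's own figures show to be mostly unobserved, while the table omits it.

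Four stronger readings are tempting, and the document does not support them.
- *The ANCOVA means would be meaningless.* With full follow-up, capping at 12 months gives a valid restricted mean. The weakness is compression near the ceiling, and bias arises from children lost before 12 months.
- *The effect would vanish.* Restricting to children weaned by 12 months would give 5.84 v 5.89 months in the 85% v 90% example. But nothing in the article proposes dropping children still breastfed, and it states intention-to-treat.
- *The 85% also undermines exclusive breastfeeding duration.* It does not. That duration is compared up to six months, which few infants reach.
- *The primary result is at risk.* The primary outcome is whether the infant was exclusively breastfed for six months, and is not analysed by ANCOVA.

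**Conclusion.** The point holds for duration of any breastfeeding. The text gives it two methods, one unsuited to an outcome with about 85% censoring, and Table 2 gives it one. The 85% follows directly from the stated 15% and the 12-month follow-up; the 86.5% rests on the constant, independent hazards assumed above.

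The differences of 0.31 and 0.58 month are illustrations. They depend on the constant hazard and on assumed contrasts (85% v 90% still breastfed; 15% v 25% attrition), none of which the article states. They show that a real effect would look small on a capped mean, and that a plausible imbalance in loss could match or exceed it if last observed time were used. The Discussion itself expects loss to follow-up because of high mobility in the slums.

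For duration of exclusive breastfeeding, only the inconsistency between text and Table 2 and the handling of loss remain. The matter is worth correcting but is confined to secondary analyses.

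**What to change.** Remove duration of any breastfeeding from the ANCOVA sentence and make the survival analysis already in Table 2 its sole analysis. State that children are censored at last contact or at 12 months, whichever comes first, and that the method allows for clustering in a way suited to 14 clusters. If a difference in months is wanted, add a restricted mean to 12 months estimated with allowance for censoring.

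For duration of exclusive breastfeeding, align the text with Table 2, so that one method is named and loss before six months is handled. ANCOVA can stay for continuous outcomes that are fully observed.

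The cost is a change of wording. No extra data, visits or participants are needed.

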### Sample size considerations

The sample size determination was done considering the study design of cluster randomisation since villages in the study sites will be randomised to either control or intervention [29]. A minimum sample size for both intervention and control arms of 196 was estimated to have enough power to detect an increase in exclusive breastfeeding for six months from two per cent (the baseline rate of exclusive breastfeeding in the study setting) [22] to 12%; a ten percentage point increase, although higher increase has been documented in similar interventions elsewhere in the developing world [30]. We used a level of precision of five per cent (for a two-sided *t*-test) and power of 80%. We then adjusted for expected intra-cluster correlation (ICC) using a design effect of 3.2. The design effect was based on an ICC of 0.05, based on previous research on breastfeeding practices in the study area which acts as a baseline for the current study. We allowed for 20% potential attrition, also based on previous research in the study area [31]. Therefore, an effective sample size of about 780 mother-child pairs was estimated. We used practice of exclusive breastfeeding to undertake the sample size calculations as it is our primary outcome of interest. (More detailed account of sample size determination is attached as an additional material in Additional file 1).

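### The primary analysis is named without any term for the 14 randomised community units; run as written, its two-sided type I error is about 17% to 29% at the plan's own ICC of 0.05

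*Protocol article*

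**What the plan says.** **Design.** Under Study design and randomization, 14 CUs (eight in Korogocho, six in Viwandani) are allocated half to each arm, after stratification by slum and by the number of women of reproductive age.

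**Sample size.** Under Sample size considerations: "We then adjusted for expected intra-cluster correlation (ICC) using a design effect of 3.2". The ICC behind this is 0.05, taken from earlier breastfeeding research in the study area.

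**Analysis.** The Statistical analysis section assigns the primary outcome, exclusive breastfeeding for six months, to "multinomial logistic regression analysis for categorical variables (that is, whether exclusively breastfed for six months or not"). For the first objective, which contains the primary outcome, Table 2 gives the analysis as "Multinomial logistic regression for rates and survival analysis for duration". The independent variable is intervention status. The control variables are socio-economic status, food security, maternal demographic characteristics, antenatal care and child morbidity. Stunting, underweight and wasting also get multinomial logistic regression, and continuous outcomes get ANCOVA.

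The one hierarchical method is placed elsewhere: "multilevel modelling for repeated measures such as diarrheal morbidity will be applied". Clusters are mentioned in the analysis text only in connection with baseline imbalance.

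**The concern.** Design and sample size treat mothers in one CU as correlated on the primary outcome, strongly enough to multiply the required sample by 3.2. The model named for that outcome has no element that carries this correlation. An analyst who followed the text would treat about 627 mothers as independent, although only seven units per arm were randomised. Standard errors would be too small and confidence intervals too narrow, and chance differences between CUs could be reported as an effect of counselling. The trial is meant to inform policy and roll-out, so a false positive on the primary outcome would matter. The same gap affects the other models in Table 2 that carry no CU term.

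**Working it through.** **Inputs** (Sample size considerations; Study design and randomization)
- "level of precision of five per cent", "for a two-sided" test; power 80%
- Rates: "from two per cent (the baseline rate of exclusive breastfeeding in the study setting") "to 12%; a ten percentage point increase"
- Total before clustering 196; design effect 3.2; ICC 0.05; attrition 20%; final size about 780
- 14 CUs, 7 per arm

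**Step 1. The plan's own figures reproduce.**
- Unpooled two-proportion formula: (1.96 + 0.842)² × (0.02×0.98 + 0.12×0.88) / 0.10² = 98.3 per arm, about 196 to 198 in total. The plan says 196.
- 196 × 3.2 = 627.2, and 627.2 / 0.80 = 784. The plan says about 780.
- 1 + (m − 1) × 0.05 = 3.2 gives m = 45 per CU, and 627.2 / 14 = 44.8. The design effect therefore fits 14 clusters after attrition.

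So the sample size does allow for clustering. The question concerns the analysis model only.

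**Step 2. Large-sample type I error of a test that omits the CU.** The naive standard error is too small by √3.2 = 1.79. The true two-sided error is 2 × [1 − Φ(1.96 / 1.79)] = 2 × [1 − Φ(1.096)] = 27.3%.

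By ICC, with m = 44.8:

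| ICC | Design effect | Type I error |
|---|---|---|
| 0.01 | 1.44 | 10% |
| 0.02 | 1.88 | 15% |
| 0.03 | 2.31 | 20% |
| 0.05 | 3.19 | 27% |
| 0.10 | 5.38 | 40% |

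**Step 3. Simulation, because events are sparse at 2%.** Beta-binomial data with no effect, 7 CUs per arm, 45 mothers per CU, at least 100,000 replicates. A Wald test with no event in one arm was counted as not rejecting.

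| Rate in both arms | ICC | Score | Likelihood ratio | Wald | t-test on CU proportions, 12 df |
|---|---|---|---|---|---|
| 2% | 0.05 | 26% | 29% | 17% | 3% |
| 5% to 30% | 0.05 | 27% to 28% | 27% to 28% | 26% to 27% | 4% to 5% |
| 2% | 0.01 | 10% | 12% | 6% | 4% |
| 5% to 30% | 0.01 | 10% | 10% | 9% to 10% | 5% |

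The first three tests ignore the CU. The t-test on CU proportions does not materially exceed 5% in any scenario.

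**Step 4. Sparse clusters.** At a 2% rate, a CU of 45 has no event with probability 0.98⁴⁵ = 0.40 without clustering, and about 0.62 at ICC 0.05. This bears on the choice of remedy.

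**Step 5. Width of intervals.** Correcting the standard error alone widens them by √3.2 = 1.79. With a t-test on 12 df the factor is 1.79 × 2.179 / 1.96 = about 2.0.

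**The case against.** The strongest objection is that the article names families of models and not variance estimators. Logistic regression can be fitted with cluster-robust standard errors, and the authors plainly know that the design is clustered. An article condenses, and a full protocol or SAP that is not shown may add the cluster term. This stands to the extent that a reader might infer that the trial has decided to ignore its clusters. The article does not say so, and the error rates are conditional on running the model as written.

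It does not remove the point. The article is not silent on the primary model: it names it in the text and in Table 2, lists its independent and control variables, and gives the hierarchical method to repeated measures. Read together, these specify a model that does not match the design.

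A second objection is that a single figure of 27% overstates the case. This stands in part. With 2% in both arms, the usual Wald test gives about 17% at ICC 0.05 and 6% at ICC 0.01, so the size must be given as a range. At ICC 0.05, the plan's own value, even the low end is more than three times nominal.

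Two further readings carry no weight. Multinomial regression for a yes/no outcome reduces to binary logistic regression and does not alter the error rate. That the levels of the diarrhoea model are not listed does not show that the CU is left out of it.

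**Conclusion.** The point holds. The design and sample size rest on clustering by CU, while the analysis named for the primary outcome includes neither the CU nor the strata. Run as written, its two-sided type I error at ICC 0.05 is about 26% to 29% with a score or likelihood-ratio test. With a Wald test it is about 17% if the rate is 2% in both arms, and 26% to 27% at rates of 5% to 30%. At ICC 0.01 the range over all three tests is about 6% to 12%.

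These figures assume 14 CUs of equal size, about 45 mothers analysed in each, no covariate adjustment and no cluster correction added elsewhere. Because this is the primary test, the text should be corrected before the analysis.

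**What to change.** State a primary analysis that respects the CU as the unit of randomisation and includes the strata (slum and size). Either of these would do:

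- **Cluster-level comparison.** Compare the 14 CU proportions, with a t-test on cluster degrees of freedom or a permutation test within strata. Where the planned covariate adjustment is kept, use covariate-adjusted cluster residuals.
- **Mixed or GEE binary logistic model**, with the CU as cluster and a small-sample correction for 14 clusters.

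Both are accepted methods. The many control CUs expected to have no event at a 2% rate are a practical argument for the cluster-level version.

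Carry the CU into the ANCOVA and survival models and those for stunting, underweight and wasting, and state it explicitly as a level of the diarrhoea model.

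**Cost.** Wording and code only, with no new data. Confidence intervals become about 1.8 times as wide, or about 2.0 times with a t-test on 12 df. The cluster-level t-test is somewhat conservative (about 3%) if the rate is 2% and the ICC 0.05.
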